### Study endpoints

#### Primary endpoints

As the pro-inflammatory cytokine IL-6 is consistently upregulated following intra-abdominal sepsis or injury and has been reported to correlate with outcomes (Table 
2), the primary endpoint is the difference in the plasma concentration of IL-6 at 24 and 48 h after dressing application between patients randomized to TAC with the ABThera™ *versus* Barker’s vacuum pack after damage control laparotomy.

#### Secondary endpoints and exploration of clinical efficacy and safety

Secondary endpoints of interest include trial feasibility (number of patients enrolled/number of eligible candidates) and the differential effects of the allocated TAC dressings on several physiological and organ dysfunction outcomes, including: (1) the plasma concentration of TNF-α and IL-1, -8, -10, and −12 at 24 and 48 h; (2) the collective peritoneal and systemic mediator profiles (see below); (3) the activation potential of peritoneal fluid
[70,71]; (4) peritoneal fluid drainage volume; (5) postoperative daily fluid balance; (6) SOFA scores and individual organ system components of these scores; (7) the PaO_2_/FIO_2_ ratio; (8) vasopressor requirements and arterial lactate levels; (9) need for renal replacement therapy; (10) RIFLE criteria; (11) APACHE-II scores; and (12) 24 h enteral tolerance (if no gastrointestinal anastomosis was performed).

Secondary clinical efficacy and safety endpoints of interest include: (1) in-hospital death; (2) fascial closure rate and days with fascial closure for the month after admission to hospital; (3) ventilator-free days for the month after admission to hospital; (4) ICU-free days from the month after admission to hospital; (5) hospital-free days from the month after admission to hospital; and (6) risk of renal replacement therapy and days free of renal replacement therapy from the month after admission to hospital. Further, as some have suggested that negative pressure peritoneal therapy may be associated with an increased risk of abdominal fistula formation or development of intra-abdominal hypertension/recurrent abdominal compartment syndrome
[72-74], additional safety outcomes include: (1) intestinal and enteroatmospheric fistula formation; (2) daily IAP; (3) daily WSACS intra-abdominal hypertension grading classification; and (4) risk of abdominal compartment syndrome development.

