### Patient randomization

To preserve allocation concealment, randomization will be performed using a random treatment generator hosted on a dedicated, publicly available trial website (http://www.peritonealvac.com/). When an eligible patient is identified by the attending surgeon, this website will be accessed by a member of the operating room team and the patient’s last name and hospital number will be entered. The random treatment allocation will then be announced such that the attending surgeon can perform the indicated method of TAC. Variable block size randomization will be performed to ensure equal numbers of patients in each treatment group. Day 1 is considered the day of randomization.

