#### Clinical data

Clinical data will be prospectively recorded at the time of enrollment and until study day 28, hospital discharge, or death. We will collect data on baseline patient demographics; past history; indication for damage control laparotomy; injury or illness severity scores (Acute Physiology and Chronic Health Evaluation-II [APACHE-II]
[63]; Sequential Organ Failure Assessment [SOFA]
[64], and Injury Severity Score [ISS]
[65,66]); fluid balance; need for renal replacement therapy and the Risk, Injury, Failure, Loss, and End-stage-kidney-disease (ESKD) (RIFLE) criteria for acute renal dysfunction
[67]; and patient physiology (arterial pH, base deficit, and lactate levels; oxygenation indices and partial pressure of arterial oxygen [PaO_2_]/fraction of inspired oxygen [FIO_2_] ratios; and gastric residual volumes). IAP will also be measured via an indwelling bladder catheter as recommended by the World Society of the Abdominal Compartment Syndrome (WSACS)
[68] every 6 h while the abdomen is open and every 12 h once it has been closed.

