### Sample size

No clinical data yet exist on the effect of negative pressure peritoneal therapy on the inflammatory response after damage control laparotomy for intra-abdominal sepsis or injury. Thus, estimates are not available to allow accurate sample size estimation. We therefore propose to undertake a study among a convenience sample of 46 adults. As there are approximately 40 to 50 patients who undergo damage control laparotomy and open abdominal management per year at our institution, this trial should be able to be completed within a 2-year time period.

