### Statistical analyses

All continuous variables will be summarized using histograms and measures of central tendency to determine their underlying distribution before statistical descriptions or analyses are conducted. Means (with standard deviations) and medians (with interquartile ranges) will be used to summarize normal and skewed data, respectively. Non-correlated means and medians will be compared using t-tests and Wilcoxon rank sum tests while dependent means and medians will be compared using paired t-tests and Wilcoxon signed rank tests. Differences in proportions will be compared using Fisher’s exact test and risk ratios with associated 95% confidence intervals.

For the analysis of the primary endpoint, we will use a mixed-effects repeated measures linear model to compare the effects of the ABThera™ and Barker’s vacuum pack on changes in plasma IL-6 concentration at 24 and 48 h after TAC dressing application
[75,76]. For longitudinal studies, mixed-effects models have previously been shown to be superior to conventional last-observation-carried-forward approaches for handling missed observations during follow-up
[77,78]. This approach will also be used to compare the plasma concentrations of TNF-α and IL-1, -8, -10, and −12 between groups at 24 and 48 h in the analysis of secondary endpoints.

Multidimensional analysis will be used to assess whether the allocated TAC dressing has an effect on the collective peritoneal and plasma mediator profiles of the study patients. Principal components analysis will be used to reduce the mediator concentration variables into a smaller set of components that account for most of the variability in the data. Component scores will subsequently be calculated along the reduced number dimensions, after which we will attempt to distinguish between patients treated with the ABThera™ and Barker’s vacuum pack using discriminant or latent class analysis. A similar approach will be performed in order to relate inflammatory mediator concentrations to outcomes.

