## Abbreviations

APACHE-II: Acute physiology and chronic health evaluation-II; ELISA: Enzyme-linked ImmunoSorbent assay; ESKD: End stage kidney disease; FIO2: Fraction of inspired oxygen; FMC: Foothills medical center; IAP: Intra-abdominal pressure; KCI: Kinetic Concepts Inc; ICU: Intensive care unit; ISS: Injury severity score; PaO2: Partial pressure of arterial oxygen; RCT: Randomized controlled trial; RIFLE: Risk injury, failure, loss, and end-stage-kidney-disease; SOFA: Sequential organ failure assessment; TAC: Temporary abdominal closure; WSACS: World Society of the Abdominal Compartment Syndrome

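### The APACHE-II total, listed as an outcome of the dressing, includes a chronic-health part that cannot respond; the unadjusted tests named for it lose some precision as a result

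*Protocol article*

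**What the plan says.** The secondary endpoints section introduces its first list as "the differential effects of the allocated TAC dressings on several physiological and organ dysfunction outcomes", and the eleventh of its 12 items reads "11) APACHE-II scores". The Clinical data section collects the same score among the "injury or illness severity scores (Acute Physiology and Chronic Health Evaluation-II [APACHE-II" measures, alongside SOFA and ISS. It adds that "Clinical data will be prospectively recorded at the time of enrollment and until study day 28", with discharge or death as earlier end points. The Abbreviations section also spells the score out as "Acute physiology and chronic health evaluation-II". Neither place gives its components or weights.

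On analysis, the Statistical analyses section gives a general rule: "Non-correlated means and medians will be compared using t-tests and Wilcoxon rank sum tests". Paired versions are named for dependent data. The mixed-effects model, which addresses changes over time, is assigned to plasma IL-6 and then to the other named cytokines. Results are also to be stratified by indication (sepsis or trauma). No adjustment of APACHE-II for its value at enrolment is described.

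The trial enrols "a convenience sample of 46 adults", and the Patient randomization section states: "Variable block size randomization will be performed to ensure equal numbers of patients in each treatment group".

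**The concern.** An outcome meant to show what a dressing does should be able to move when the dressing works. Chronic health cannot: it is what the patient brought to the operating room. When the whole score is compared between arms, any effect on acute physiology has to be seen against variation in chronic disease as well. In a small trial that the Discussion already concedes may be underpowered, this noise is avoidable. The Discussion also plans to use the results as pilot information for a multicentre trial, so the precision of estimates matters as well as the tests.

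**Working it through.** **Inputs from the Protocol article.** Total sample 46 (Sample size); equal groups (Patient randomization), hence 46/2 = 23 per arm. The article states no standard deviation, effect size or power, so it has no figure of its own to reproduce for this endpoint.

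**Assumed inputs.** SD of the fixed part 2 to 4 points; SD of the total score 7 to 8 points; fixed and acute parts uncorrelated; no baseline adjustment. None of these comes from the documents.

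**Step 1: share of variance that cannot respond.** f = SD_fixed² / SD_total².
- Smallest: 2²/8² = 4/64 = 6%.
- Largest: 4²/7² = 16/49 = 33%.

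**Step 2: standard error of the difference between arms.** SE = SD × sqrt(2/23) = 0.295 × SD.
- Smallest share: total 8 × 0.295 = 2.36 points; acute part alone sqrt(64 − 4) × 0.295 = 7.75 × 0.295 = 2.28 points.
- Largest share: total 7 × 0.295 = 2.06 points; acute part alone sqrt(49 − 16) × 0.295 = 5.74 × 0.295 = 1.69 points.

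The ratio is 1/sqrt(1 − f), which is 1.03 at the low end and 1.22 at the high end. The total's standard error is therefore about 3 to 22% larger than that of the part that can respond. As equivalent sample size for this endpoint, 1/(1 − f) gives 1.07 to 1.48.

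**Step 3: what that does to power.** Let d be the effect in SDs of the acute part. Using the total shrinks it to d × sqrt(1 − f). Power (normal approximation, two-sided 0.05, before false discovery rate correction) is Φ(d × sqrt(1 − f)/0.295 − 1.96).

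| Assumed d | f = 0 | f = 0.10 | f = 0.25 |
|---|---|---|---|
| 0.5 | 40% | 36% | 31% |
| 0.8 | 77% | 73% | 65% |
| 1.0 | 92% | 90% | 84% |

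**Step 4: is the test still valid?** A simulation with no dressing effect, 23 per arm and a binary fixed component (assumed prevalence 0.2) gave these rejection rates at nominal 5%:

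| Fixed share f | t-test (40,000 runs) | Wilcoxon (5,000 runs) |
|---|---|---|
| 0 | 5.1% | 4.8% |
| 0.10 | 5.0% | 4.9% |
| 0.25 | 5.0% | 4.3% |
| 0.50 | 4.9% | 4.5% |

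The false-positive rate does not rise with the fixed share. The cost is precision only.

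**The case against.** Two stronger readings are tempting, and the documents support neither.

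A reader might infer that a chance excess of chronic disease in one arm would be mistaken for a treatment effect. Such imbalance can certainly arise: with an assumed comorbidity prevalence of 10 to 40%, the arms would differ by four or more patients in 8 to 29% of trials. But allocation is randomised, so imbalance is part of the random error that the test's standard error already contains, as step 4 confirms. A single estimate can be shifted by it, as can any endpoint that depends on prognosis in a small trial. The per-protocol set could weaken this protection, but the Statistical analyses section reserves that set for mediator data.

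A reader might also infer that a score cannot be both a severity descriptor and an outcome. It can: a value at entry may describe case mix and serve as a covariate for a later value. SOFA has the same two roles in this article.

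The best remaining objection is that an article may leave the time point, derivation and covariates of one secondary endpoint to the full protocol or analysis plan, neither of which is shown. If change from enrolment were compared, the fixed points would cancel; adjustment would remove much of them. That stands as a limit: missing detail is not the complaint here. The point rests on what the article does state, namely the score as an outcome and unadjusted tests for it. It is also fair that the assumed SDs have no source in the documents, that the upper figure pairs the largest fixed SD with the smallest total SD, and that acute physiology is already covered by SOFA, oxygenation, vasopressors, lactate and RIFLE in the same list.

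**Conclusion.** The point holds as a minor matter of precision. The APACHE-II total includes a part that the dressing cannot affect, and the stated unadjusted tests leave that variation in the comparison. The inflation of the standard error, about 3 to 22%, depends wholly on the assumed 6 to 33% fixed share, on uncorrelated parts and on no baseline adjustment. That the loss exists needs only some variation in chronic health between patients and parts that do not offset each other. Validity is not in question for a comparison of patients as randomised. This is one of many secondary endpoints and no trial decision hangs on it, so the case for acting is that the remedy is cheap.

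**What to change.** In the secondary endpoints section, define item 11 as the score measured after dressing application, preferably its acute physiology part. In Statistical analyses, compare it between arms with adjustment for the enrolment value (for example, linear regression on arm and enrolment value). Keep the total at enrolment as a baseline descriptor under Clinical data. If the total is retained as the outcome, adjusting for its enrolment value still recovers much of the loss.

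The Clinical data section has recording run from enrolment onward, so an enrolment value should be on hand. The article does not say that the score's components are stored separately, so this should be confirmed before choosing the physiology-only version.

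There are two costs. The physiology-only score is less familiar to readers than the total. The definition would also change late: Trial status reports 37 of 46 patients enrolled (37/46 = 80%), so the change should be dated, made before any comparison by arm, and reported as an amendment.

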### Patient recruitment

Recruitment into the trial will occur in the operating room once the decision has been made by the attending trauma or general surgeon to perform a damage control laparotomy and TAC. We will define an open abdomen as that requiring a TAC due to the abdominal skin and fascia not being closed after laparotomy.

Although no objective, evidence-based indications for damage control laparotomy or open abdominal management exist
[60,61], the Eastern Association for the Surgery of Trauma suggest that this technique may be considered in cases of severe abdominal trauma involving hepatic, non-hepatic, or vascular injuries with intra-abdominal packing; among trauma patients with acidosis (pH ≤7.2), hypothermia (temperature ≤35°C), and clinical coagulopathy or if the patient is receiving massive transfusion; and in patients with severe intra-abdominal infection/peritonitis or necrotizing pancreatitis
[59]. Other indications for the procedure suggested in 2005 by a multidisciplinary expert advisory panel on management of the open abdomen included bowel edema and a significant risk of developing abdominal compartment syndrome
[62].

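### Free-day and fascial-closure endpoints are counted over an undefined month from hospital admission, whereas study days and clinical data run from randomisation to at most study day 28

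*Protocol article*

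**What the plan says.** In the Protocol article, the section on secondary endpoints and exploration of clinical efficacy and safety ties five day-count endpoints to hospital admission:

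- "fascial closure rate and days with fascial closure for the month after admission to hospital"
- "ventilator-free days for the month after admission to hospital"
- "ICU-free days from the month after admission to hospital"
- "hospital-free days from the month after admission to hospital"
- "days free of renal replacement therapy from the month after admission to hospital"

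It does not say how many days make a month. The same list includes in-hospital death with no time limit.

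The trial's own clock starts later. Under Patient recruitment: "Recruitment into the trial will occur in the operating room once the decision has been made". Under Patient randomization: "Day 1 is considered the day of randomization". Under Clinical data: "Clinical data will be prospectively recorded at the time of enrollment and until study day 28, hospital discharge, or death". The inclusion and exclusion criteria set no limit on the time from admission to the index laparotomy.

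**The concern.** The endpoints run on an admission clock and the data on a randomisation clock. The two agree only for patients randomised on the day of admission, and then only if the month is taken as 28 days counted from that day.

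For anyone admitted earlier, the score includes days that were settled before the dressing was allocated, and the effect differs by endpoint. Inpatient days off the ventilator before the operation add to ventilator-free days. Inpatient days before the operation cannot be hospital-free, so they lower the highest attainable number of hospital-free days. Days with fascial closure have no clear meaning before the index laparotomy. The number of days on which the dressing could matter also varies from patient to patient.

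This matters because the Discussion says the trial is to inform the design of a multicentre trial of clinical outcomes. Free-day estimates that mix time before and after allocation are a poor basis for that.

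**Working it through.** The plan gives no figure to reproduce here: the 46 patients are a convenience sample with no calculation behind them. The check is a day count.

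**Inputs**
- Study day 1 is the day of randomisation (Patient randomization).
- Recording runs from enrolment to study day 28 at the latest (Clinical data).
- d is the number of days from admission to randomisation. The document does not give it; 0 to 30 is an assumed range.
- M is the length of the month in days. It is not stated; 28, 30 and 31 are assumed values.

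**Formulas, with the admission day as window day 1**
- Admission falls on study day 1 − d, so the window covers study days 1 − d to M − d.
- Scored days before allocation = min(d, M).
- Scored days past study day 28 = max(0, M − d − 28).

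**Results** (days before allocation / days past study day 28)

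| d | M = 28 | M = 30 | M = 31 | Days within study days 1–28, M = 30 |
|---|---|---|---|---|
| 0 | 0 / 0 | 0 / 2 | 0 / 3 | 28 |
| 1 | 1 / 0 | 1 / 1 | 1 / 2 | 28 |
| 2 | 2 / 0 | 2 / 0 | 2 / 1 | 28 |
| 3 | 3 / 0 | 3 / 0 | 3 / 0 | 27 |
| 7 | 7 / 0 | 7 / 0 | 7 / 0 | 23 |
| 14 | 14 / 0 | 14 / 0 | 14 / 0 | 16 |
| 30 | 28 / 0 | 30 / 0 | 30 / 0 | 0 |

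With M = 30, the share of scored days before allocation is 7/30 = 23% at d = 7 and 14/30 = 47% at d = 14. At d = 30 nothing after allocation is scored.

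**If the window starts the day after admission**, there is one day fewer before allocation (for d of 1 or more, while the window still reaches past allocation). The excess past study day 28 becomes max(0, M − d − 27). At d = 0 that is 1, 3 or 4 days for M = 28, 30 or 31. It reaches zero at d = 1, 3 or 4.

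Across both conventions, the largest excess is therefore 2 to 4 days for a 30- or 31-day month, and it has gone by d = 2 to 4. The two mismatches trade off: days before allocation grow with d, while the tail past day 28 shrinks.

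**With the window set to study days 1 to 28**, there are 0 days before allocation and 0 days past day 28 for every d.

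**The case against.** The strongest reply is that little is shown to be at stake. Patients are enrolled at an emergency index laparotomy, so short gaps are plausible for many, and for a same-day admission no more than hours precede allocation. Nothing in the article says how long the gap is, for sepsis or for trauma. This stands: the size of the problem cannot be stated from the document.

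Four stronger readings are tempting, and the text does not support them.

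- *Bias between arms through indication.* A reader might infer that septic patients operated on late distort the comparison. Indication and time since admission both precede a randomised allocation, so they balance in expectation, and results are also stratified by indication. If d did differ by indication, the two strata would have different post-allocation exposure, but that is not bias between dressings.
- *Every patient is affected both ways.* The table shows that the two mismatches largely exclude each other.
- *The data do not exist.* The Clinical data section describes prospective recording. It does not rule out reading earlier inpatient days from the hospital chart.
- *Late in-hospital deaths are missed.* This follows only if recording stops at the earliest of the three listed events. The blood-sampling text says explicitly that the earlier of two events applies; the clinical-data sentence does not. Because in-hospital death is a named endpoint, following vital status to discharge is a natural intent. The text should settle it.

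None of this removes the central point. The article states both windows, and they do not match, so this is not detail left to a fuller document.

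**Conclusion.** The point holds in a limited form. The five endpoints are anchored at admission over a month of unstated length, while study days and recording are anchored at randomisation and end by study day 28. For a patient admitted d days before randomisation, up to d scored days cannot respond to the dressing. For d of about 0 to 3, a 30- or 31-day month overruns the recording limit by at most 2 to 4 days. Both the month length and the range of d are assumptions.

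The consequence is added noise, dilution of any effect, and possible chance imbalance in d with 46 patients. It is not systematic bias. It concerns secondary endpoints only: the primary IL-6 endpoint is timed from dressing application and is unaffected. The change is still worth making, because it is specific, removes both mismatches for every gap, and costs little.

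**What to change.** 1. In the secondary endpoints section, define days with fascial closure and ventilator-, ICU-, hospital- and renal-replacement-free days from randomisation (study day 1) through study day 28.
2. In the Clinical data section, state that vital status is captured to hospital discharge even when that falls after study day 28, so that recording matches the in-hospital death endpoint.
3. Document the change as an amendment before final analysis. The Trial status section reports 37 patients enrolled, leaving 46 − 37 = 9 to recruit, and surgeons know the allocation. The date and reason should therefore be on record.

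**Cost.** This is more than a change of wording. If recording stops at an earlier discharge, complete hospital-free days need a day-28 status or readmission check for those patients. Results will also be less comparable with reports that count from admission.
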